## 4. Conclusions

Spatial navigation is a complex cognitive ability that is essential for the independence, quality of life, and safety of the elderly. Spatial navigation has been reported to be one of the first cognitive domains to be affected in AD, which occurs as a result of progressive neuropathology involving specific brain areas. Thanks to the use of a comprehensive assessment (i.e., virtual and naturalistic evaluation) implemented by an advanced technological apparatus, our research protocol constitutes an innovative method of investigating SN performances in participants at increased risk of developing AD, potentially revealing the employment of compensatory strategies of navigational guidance able to resist neuropathological damage, and may suggest the definition of specific cognitive remediation techniques in order to improve visuospatial skills. Findings will be disseminated through scientific articles as well as attendance at national and international congresses or academic lectures/seminars/workshops.

## Figures and Tables

**Figure 1 jpm-14-00192-f001:**
[figure not shown]
On the left, a representation of egocentric navigation based on the navigator; on the right, a representation of allocentric navigation based on the relationships among landmarks (designed by Freepik).

**Figure 2 jpm-14-00192-f002:**
[figure not shown]
An example of a PPI virtual task: The navigator has to reach a destination point from a start position (black route). When he/she arrives, he/she is asked to come back to the start point without using any external support, potentially travelling many different routes, for example, red/blue routes (designed by Freepik).

**Figure 3 jpm-14-00192-f003:**
[figure not shown]
An anatomical illustration of brain areas supporting spatial navigation (designed by Freepik).

**Figure 4 jpm-14-00192-f004:**
[figure not shown]
General planimetry of the Pontificio Istituto Missioni Estere (PIME, [name]) with the experimental ecological task: the Detour Navigation Test—modified version (DNT-mv) on the outdoor urban garden. B1= first option for Route B retour; B2= second option for Route B retour; B3= third option for Route B retour.

**Figure 5 jpm-14-00192-f005:**
[figure not shown]
PIME landmarks: hits in the left column; distractors in the right column. (**A1**–**F1**) correct landmarks; (**A2**–**F2**) distractors similar to the landmarks.

**Figure 6 jpm-14-00192-f006:**
[figure not shown]
Howdy Senior system components. The electronic unit (white) detects heart rate, respiratory rate, and body position. It is equipped with five automatic snaps on the back and communicates with the Howdy app via Bluetooth. The electronic unit can be combined with different textile units: male/female top with sensors and belt. The electronic unit and textile unit are connected using the automatic snaps. The Howdy Apps works on smartphones and tablets running Android 8.0 or later.

**Table 1 jpm-14-00192-t001:** Cardiac, respiratory, and accelerometer parameters collected by the Howdy Senior App.

**Cardiac system functions** *Time domain over RR intervals parameters*	avgRR: mean of R2R interval; SDRR: standard deviation of R2R interval; avgHR: mean of Heart rate; SDHR: standard deviation of Heart rate; MSSD: mean of square successive differences between normal heartbeat; RMSSD: root mean square of square of successive differences between normal heartbeat; lnRMSSD: natural log of RMSSD; hrvScore: normalized lnRMSSD value using as scaling factor the value 6.5; RR50: number of successive absolute difference greater than 50 ms; pRR50: percentage of number of successive absolute difference greater than 50 ms over the number of elements in the analyzed window; SD1: standard deviation along the minor axes of the Poincare plot; SD2: standard deviation along the major axes of the Poincarè plot; Stress index.
**Cardiac system functions** *Frequencies domain over RR intervals parameters*	LF: power in the low frequency band affected by sympathetic nervous system (SNS); HF: power in the high frequency band affected by parasympathetic nervous system (PNS); LF/HF: ratio between the power in low and high frequency band.
**Respiratory system functions**	avgBR: mean of BR; SDBR: standard deviation of BR.
**Accelerometer parameters**	AccXavg, AccYavg, AccZavg: mean of accelerations for X, Y, Z axes; AccXsd, AccYsd AccZsd: standard deviation of accelerations for X, Y, Z axes; AccXrms, AccYrms, AccZrms: root mean square of accelerations for X, Y, Z axes.

The Howdy Senior system has been recently implemented by the “Aptive” App capable of recording GPS data during the naturalistic experiment. These data include “Time” as the number of minutes to complete the route; “Latitude”, “Longitude”, “Altitude”, and “Speed” as estimated by the body integrated accelerometer for calculating steps variability; and “Direction” corresponding to gait orientation with values ranging from 0° to 360°, where 0° corresponds to the north, 90° to the east, 180° to the south, and 270° to the west. Thanks to the Aptive App, a GPX tracking of participants’ body movements around the urban environment will be registered, too.

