## Abstract

Spatial navigation (SN) has been reported to be one of the first cognitive domains to be affected in Alzheimer’s disease (AD), which occurs as a result of progressive neuropathology involving specific brain areas. Moreover, the epsilon 4 isoform of apolipoprotein-E (APOE-ε4) has been associated with both sporadic and familial late-onset AD, and patients with mild cognitive impairment (MCI) due to AD are more likely to progressively deteriorate. Spatial navigation performance will be examined on a sample of 76 community-dwelling senior citizens (25 healthy controls; 25 individuals with subjective cognitive decline (SCD); and 26 patients with MCI due to AD) via a virtual computer-based task (i.e., the AppleGame) and a naturalistic task (i.e., the Detour Navigation Test—modified version) for which a wearable device with sensors will be used for recording gait data and revealing physiological parameters that may be associated with spatial disorientation. We expect that patients with MCI due to AD and APOE-ε4 carriers will show altered SN performances compared to individuals with SCD and healthy controls in the experimental tasks, and that VR testing may predict ecological performance. Impaired SN performances in people at increased risk of developing AD may inform future cognitive rehabilitation protocols for counteracting spatial disorientation that may occur during elders’ traveling to unfamiliar locations. The research protocol has been approved by the Ethics Committee of the Istituto Auxologico Italiano. Findings will be published in peer-reviewed medical journals and discussed in national and international congresses.

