### 2.4. Statistical Analysis

Data distribution will be first checked on collected variables by assessing skewness and kurtosis values, by performing normality and heteroscedasticity tests, and by visually inspecting histogram and Q–Q plots. Based on data meeting or non-linear model assumption, either parametrical or non-parametrical analyses will be performed. By means of the R marco *pwr* [86], the minimal sample size has been set as 76 participant, based on a power analysis for a multiple regression model that took into account the following parameters: α = 0.05; 1-β = 0.9; *f*^2^ = 0.15 (medium effect size, in order to be conservative) [87]; and numbers of predictors: 3 (age, APOE genotypes, and belonging to each group, with the last two predictors as dummy variables).

We will detect the route disorientation scores, i.e., WTs and MsH, as already described in Puthysserypaddy et al. [64]. Accordingly, all the violations in terms of deviations from the pre-established return path (i.e., movement at an intersection onto a different path as compared to the original one, or non-roadable walkways) will be written down by the experimenter as WTs in a pre-set paper grid for *Route A*. The overlaps with the *Route A* return path, and, likewise, non-roadable walkways will be written down by the experimenter as WTs in a pre-set paper grid for Route *B*. Further, we will detect the MsH as the participant either slows down/stops and looks around to aid orientation or verbally admits to the experimenter that he/she is unsure about his/her whereabouts, both for *Route A* and the *Route B* return path.

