In addition to the experimenter visually identifying and recording the frequency of the MsH with a stopwatch and a pre-set paper grid, we will measure this variable more objectively using the Howdy Senior integrated accelerometer. For this purpose, we will use the motion sensor of the sensorial body measuring the individual’s linear acceleration in the three axes (i.e., x, y, z). To segment the magnitude signals, according to Schaat et al. [88], we will adopt time intervals of 10 s, with an overlap of 5 s between subsequent intervals because a 10 s segment is sufficiently long to capture multiple steps during walking, thus revealing important behavioral changes. In this way, we will detect the MsH as a signal flattened along the three axes. Further, given that physiological parameters may alter depending on the MsH, we will also investigate the relationship between step variability and co-occurring time-dependent cardiac and respiratory parameters detected by the Howdy App, expressed as mean values, via Pearson’s correlation coefficients or their non-parametric equivalent (i.e., Spearman’s rank order correlation). Moreover, we will run a one-way ANOVA (or its non-parametric equivalent) to compare performances of the three subgroups on gait parameters collected through the Aptive app and the SSNC questionnaire. In order to explore potential association between specific neurocognitive functions and SN impaired abilities, Pearson correlations or their non-parametric equivalent (i.e., Spearman’s rank order correlation) will be further performed between the AppleGame/DNT-mv results and the neuropsychological tests used in the sending centers, especially visual–constructive skills and executive functions (see Appendix A). Given the difference of the neuropsychological battery used in the sending centers, we will group tests according to the primary cognitive domain involved and we will divide the scores obtained in a dichotomous way for each participant according to the reported cut-off values in the test manuals, i.e., 0 = pathological performance; 1 = normal performance.

Finally, a linear/generalized linear regression analysis will be run, taking into account the drop errors of the AppleGame subtasks—considered one at a time—as independent variables, and the total number of “wrong turns” (WTs)/total number of “moments of hesitation” (MsH) (in seconds) of the DNT-mv as dependent variables.

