## 3. Discussion

In relation to the first endpoint, we expect that patients with MCI due to AD will show significantly more SN deficits than healthy controls and individuals with SCD, both in the AppleGame and in the DNT-mv, in terms of higher drop errors on BPI, LPI, and PPI and higher amounts of WTs and MsH, respectively. Virtual and ecological deficits may reflect a cognitive inefficiency of the entorhinal cortex, where AD neuropathology manifests early [25]. It has also been demonstrated that virtual and ecological SN tasks can detect the SN alteration of amyloid-positive MCI patients [89,90]. According to Colmant et al. [91], we also presume that APOE-ε4 carriers will report a PPI deficit in the VR task differently from non-carriers, regardless of subgroup.

Furthermore, we also anticipate that significant physiological parameters modifications (particularly, respiratory function) may be particularly associated with MsH, given that anxiety rather than depression significantly influences SN abilities in non-demented elders [92]. Starting from difficulties in spatial orientation evaluated in naturalistic experiments able to modify gait [93], we finally assume that patients with MCI due to AD will perform worse than SCD and healthy controls in terms of “Time” and “Speed”, and report significant differences in “Direction”, all variables collected by the Howdy Aptive app in the open-space naturalistic task.

In relation to the second endpoint of the research, we assume that the drop errors obtained in the VR task may predict the route disorientation scores of the naturalistic task. In particular, we expect a causal relationship between the BPI drop error of the AppleGame and the *Route A* return path of the DNT-mv, as well as between the LPI drop error of the AppleGame and the *Route B* return path of the DNT-mv, because they mainly rely on egocentric and on allocentric navigation, respectively. A recent systematic review and meta-analysis [44,94] has outlined that the association of navigational tasks performed in virtual and real environments needs to be deeply clarified. In light of this, we believe that the AppleGame could represent a validated technique with which to detect, in laboratory, early SN deficits in populations at risk of dementia conversion to provide high-quality, time-limited diagnosis. It is a cost-effective tool able to predict real-life SN impairment that should be routinely used in clinical practice.

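### Direction is a 0–360° compass bearing, but the only test stated for the Aptive gait parameters is one-way ANOVA or its rank equivalent, which does not suit raw bearings

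*Protocol article*

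**What the plan says.** Three statements in the protocol article bear on this.

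- **Scale.** The text on the Aptive app that follows Table 1 describes Direction as "corresponding to gait orientation with values ranging from 0° to 360°, where 0° corresponds to the north", with east at 90°, south at 180° and west at 270°. The same text says that a GPX track of the participant's movement is recorded.
- **Hypothesis.** Section 3 (Discussion) expects patients with MCI due to AD to do worse on Time and Speed and to "report significant differences in “Direction”, all variables collected by the Howdy Aptive app in the open-space naturalistic task".
- **Test.** Section 2.4 states: "we will run a one-way ANOVA (or its non-parametric equivalent) to compare performances of the three subgroups on gait parameters collected through the Aptive app".

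Section 2.4 also gives the rule for choosing between test families. After checks of skewness, kurtosis, normality and heteroscedasticity, "either parametrical or non-parametrical analyses will be performed". The article names no circular method and no conversion of the bearing to a linear measure.

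**The concern.** A bearing has no natural start or end, since 0° and 360° are the same heading. ANOVA works on arithmetic means. The arithmetic mean of 350° and 10° is 180°, due south, for two people who both walked almost due north. Moving to ranks does not help, because the ranks also depend on the arbitrary zero at north. The checks that trigger the switch to ranks concern distributional shape and spread, not circularity.

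What is at stake is the stated expectation about Direction in the MCI group. Applied to raw bearings, the planned test could miss a real difference, report it in the wrong direction, or report a shift in heading when one group only walks more erratically. The last is plausible in disoriented walkers. Section 2.3.2 has participants walk Route A out and back and then choose among three Route B alternatives, so headings may well span much of the circle. The route bearings themselves are in Figure 4, which is not available here.

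**Working it through.** The plan gives no figure for Direction, so there is none to reproduce. The check asks how the stated tests behave on the stated scale.

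**Inputs from the document.** Group sizes come from the Abstract: "25 healthy controls; 25 individuals with subjective cognitive decline (SCD); and 26 patients with MCI due to AD". Alpha is 0.05, taken from the sample-size paragraph of Section 2.4, which is not specific to Direction.

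**Assumptions, not in the document.** One bearing per person, normal around the group's heading and wrapped to 0–360°; SD 20°; the MCI group shifted by 15°; and the centre of the headings, which is varied.

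**Step 1: arithmetic mean against circular mean.** For 350°, 355°, 5° and 10° the arithmetic mean is 720/4 = 180° (south). The circular mean, atan2(Σ sin, Σ cos), is 0° (north).

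**Step 2: what happens to the group means.** For a true heading μ a little east of north, the share of readings that wrap to just below 360° is Φ(−μ/SD). The expected arithmetic mean is therefore μ + 360·Φ(−μ/SD).

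- Unshifted groups at 20°: 20 + 360 × 0.1587 = 77.1°.
- MCI at 35°: 35 + 360 × 0.0401 = 49.4°.

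MCI is truly 15° higher but appears about 28° lower.

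**Step 3: power for the 15° shift.** Far from north there is no wrapping and ordinary theory applies. The noncentrality is (15/20)² × (26 × 50/76) = 9.62, which with F(2, 73) gives power of 0.78. Simulation (2,000 to 4,000 runs per cell) gives:

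| Centre of headings | ANOVA | Kruskal-Wallis |
|---|---|---|
| 90° or 180° | 78–79% | 75–78% |
| 300° | 54% | 69% |
| 0° (north) | 48% | 14% |
| 20° | 11% | 16% |

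At 0° and at 20° the arithmetic means run against the true shift: about 180, 180 and 97 at 0°, and about 77, 77 and 50 at 20°.

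**Step 4: size of the tests.** With identical distributions in all groups, both tests reject in 4–6% of runs, including with headings centred on north.

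**Step 5: equal headings, unequal scatter.** Two groups have SD 20° and one has SD 40°, all with the same true heading. Centred on 180°, rejection is about 6% (ANOVA) and 5% (Kruskal-Wallis). Centred on 30°, it is about 53–55% and 51%. The formula in Step 2 explains this: 30 + 360·Φ(−1.5) = 54.1° against 30 + 360·Φ(−0.75) = 111.6°. Scatter alone separates the means by more than 57°.

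**Step 6: a circular test on comparable data.** This check used von Mises headings, 3,000 runs per scenario, a 25° shift in one group and concentration 4 (again assumed). ANOVA power was 84% at 180°, 52% at 0° and 19% at 20°. The Watson-Williams test had 84–85% at all three. With one common heading but concentrations 10/10/2, Watson-Williams rejected in 5.5–6.1% of runs, against 49% for ANOVA at 20° and 76% at 30°.

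**The case against.** The strongest reply is that the link to raw bearings is inferred. The sentence on ANOVA refers to Aptive gait parameters collectively and does not name Direction. The article does not say how a participant's stream of headings becomes one value. A condensed article may leave that to a fuller plan, and a linear summary such as heading deviation would make ANOVA usable. It stands that the per-person summary is unknown. It does not remove the point. The article defines the variable as a bearing, lists it among the Aptive outcomes expected to differ, and states one test for those outcomes. Read together, these lead to a linear test on a circular scale.

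Three stronger readings are tempting, and the document does not support them.

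- A reader might infer that the tests are invalid outright. They are not: under identical distributions both hold about 5% (Step 4).
- A reader might infer that power is lost wherever the garden lies. It is not: with headings around 90° or 180° there is essentially no loss. Since the route bearings are not available here, the actual loss is unknown.
- A reader might infer that the study's main comparisons are compromised. They are not: Direction does not enter the sample-size calculation, the drop-error, wrong-turn or hesitation scores, or the regression for the second endpoint.

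**Conclusion.** The point holds as a mismatch between a stated scale and a stated test, at moderate severity. As written, ANOVA or its rank equivalent on raw Direction gives answers that depend on where headings fall relative to north, and it can turn a difference in scatter into an apparent difference in heading. In the illustration, ANOVA power for the same 15° shift ranges from about 79% down to 11%, and Kruskal-Wallis power from about 78% down to 14%. The false signal from scatter alone ranges from about 5–6% up to 51–55%.

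These sizes rest on the assumed SD, shift, single bearing per person and choice of centres. They show how the tests can behave and do not forecast this study's result. One supporting gait hypothesis is affected.

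**What to change.** State in Section 2.4 that ANOVA and Kruskal-Wallis will not be applied to raw Direction, and fix one of two routes before the data are analysed.

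1. **Preferred: a linear measure per participant and route**, derived from the GPX track already recorded. Examples are the mean absolute heading deviation (0–180°) from the bearing of the prescribed segment, or the circular variance of heading. Compare it between groups by the one-way test already planned. Route B has three alternatives, so the reference bearing there needs a stated rule.
2. **If mean bearing is kept:** use a circular method, such as the Watson-Williams test or regression on the sine and cosine of the bearing. Say how each person's readings are reduced to one bearing.

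The Discussion should then state the expectation in terms of the chosen measure. The cost is one derived variable and a little analysis code. No new data or visits are needed.

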## Data Availability

The datasets presented in this article are not readily available because they are part of an ongoing study.

## Appendix A

**Table A1 jpm-14-00192-t0A1:** Neuropsychological tests used in the recruiting centers.

	“San Gerardo” Hospital Monza, Italy	“Luigi Sacco” Hospital Milan, Italy	Policlinico Hospital, Milan, Italy
**Global cognition**	Mini Mental State Examination (Magni et al., 1996) [98]	Mini Mental State Examination (Foderaro et al., 2022) [99] or Montreal Cognitive Assessment (Aiello et al., 2022) [100]	Mini Mental State Examination (Magni et al., 1996) [98]
**Memory** ** *Short-term memory auditory–verbal* **	Digit span backward (Monaco et al., 2013) [101] Digit span forward (Monaco et al., 2013) [101]		Digit Span Backward (Monaco et al., 2013) [101] Digit Span Forward (Monaco et al., 2013) [101]
** *Visuospatial* **			Corsi Span Backward (Monaco et al., 2013) [101] Corsi Span Forward (2013) [101]
** *Long-term memory auditory–verbal* **	List of semantically related words (Mauri et al., 1997) [102]	Free and Cued Selective Reminding Test (Girtler et al., 2015) [103]	Pairs Associate Learning (Normative data of the Hospital) Memory of prose (Normative data of the Hospital)
** *Visuospatial* **	Rey–Osterrieth Complex Figure (Caffarra et al., 2002) [104]—recall Corsi learning suvra-span (Spinnler e Tognoni, 1987) [105]	Rey–Osterrieth Complex Figure (Caffarra et al., 2002) [104]—recall Corsi learning suvra-span (Spinnler e Tognoni, 1987) [105]	Corsi learning suvra-span (Spinnler e Tognoni, 1987) [105]
**Language** ** *Comprehension* **	Neuropsychological Examination for Aphasia (ENPA)—words and sentences comprehension test (Capasso and Miceli, 2001) [106]		Token Test (Spinnler e Tognoni, 1987) [105]
** *Naming* **		Naming colored pictures (Catricalà et al., 2013) [107] Naming figures (Catricalà et al., 2017) [108]	Naming colored pictures (Catricalà et al., 2013) [107]
** *Fluency* **	Phonemic Fluency Test and Semantic Fluency Test (Costa et al., 2014) [109]	Phonemic Fluency Test and Semantic Fluency Test (Costa et al., 2014) [109]	Phonemic Fluency Test and Semantic Fluency Test (Costa et al., 2014) [109]
**Visual–constructive skills** **Visual–perceptive functions**	Rey–Osterrieth Complex Figure (Caffarra et al., 2002)—copy [104]	Clock Drawing Test (Caffarra et al., 2011) [110] Rey–Osterrieth Complex Figure (Caffarra et al., 2002)—copy [104]	Clock Drawing Test (Caffarra et al., 2011) [110]
**Visual agnosia**			Street’s Completion Test (Spinnler e Tognoni, 1987) [105]
**Constructive apraxia**			Constructive Apraxia Test (Spinnler e Tognoni, 1987) [105]
**Attention** ** *Selective* **	Visual Search Test (Spinnler e Tognoni, 1987) [105]	Visual Search Test (Della Sala et al., 1992) [111]	Visual Search Test (Spinnler e Tognoni, 1987) [105]
** *Attention/executive functions* **		Trail Making Test (Siciliano et al., 2019) [112] Stroop Color Word Interference Test (Caffarra et al., 2002) [113]	Trail Making Test (Siciliano et al., 2019) [112]
**Executive functions** ** *Global executive efficiency* **	Frontal Assessment Battery (Apollonio et al., 2005) [114]		Frontal Assessment Battery (Aiello et al., 2022) [115]
** *Verbal Fluency* **	Phonemic Fluency Test (Costa et al., 2014) [109]	Phonemic Fluency Test (Costa et al., 2014) [109]	Alternate Fluency Test (Costa et al., 2014) [109] Phonemic Fluency Test (Costa et al., 2014) [109]
** *Planning and organization* **	Rey–Osterrieth Complex Figure (Caffarra et al., 2002)—copy [104]	Rey–Osterrieth Complex Figure (Caffarra et al., 2002)—copy [104]	
** *Logical reasoning* **	Colored Progressive Matrices (Basso et al., 1987) [116]	Colored Progressive Matrices (Carlesimo et al., 1996) [117]	Colored Progressive Matrices (Basso et al., 1987) [116]
